## Abstract

**Introduction::**

Socheongryong-tang (SCRT) is an herbal medicine with anti-inflammatory and anti-allergic properties, commonly used in East Asian countries to reduce rhinitis symptoms. There have been several clinical studies of its effects on allergic rhinitis (AR), but no trials comparing it with conventional treatment. We present the protocol for a feasibility trial to assess the safety and clinical effectiveness of SCRT in AR in comparison with cetirizine.

**Methods and analysis::**

This is a randomized, open-label, cetirizine-controlled clinical trial. A total of 30 AR patients who have signed informed consent forms will be recruited and randomly assigned to SCRT or cetirizine groups at a 1:1 ratio. The participants will visit the clinical research center every week and receive SCRT granules or cetirizine tablets. SCRT will be taken twice daily, cetirizine will be taken once daily, and treatment medication will be taken for 2 weeks. Data will be collected at baseline, at week 2, and at week 4 after random allocation. The primary outcome will be the mean change in the total nasal symptom score from baseline to week 2. Secondary outcome measures will include the mini Rhinoconjunctivitis Quality of Life Questionnaire and total serum immunoglobulin E. To assess the safety of SCRT, a liver and renal function test will be conducted before and after treatment, and the participants will be asked about any occurrence of adverse events at every visit. The recruitment rate, completion rate, and medication adherence will also be calculated to assess feasibility.

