### Trial design and setting

2.2

This is a randomized two-parallel-arm open-label cetirizine-controlled comparative effectiveness study. This study will be conducted at Woosuk Korean Medicine Medical Center, Jeonju, Republic of Korea. The study has 2 arms: the SCRT treatment group and the cetirizine control group. A total of 30 participants will be recruited for this trial. Cetirizine will be used as an active control to compare the effectiveness of SCRT on AR patients whose symptoms are not controlled by conventional medication. The total study period will be 5 weeks. It consists of a week run-in period after screening, 2 weeks of medication, and 2 weeks of follow-up after medication is stopped.

The detailed design is summarized in Fig. 1 and Table 1. The study protocol (version 1.3) follows the Standard Protocol Items: Recommendations for Interventional Trials (SPIRIT) guidelines (see Additional File 1).

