#### Primary outcome

2.6.1

The primary outcome is the change in total nasal symptom score (TNSS). TNSS will be recorded in participants’ diaries every day before bedtime using a mobile application. A 4-point severity scale (no symptoms, 0; mild, 1; moderate, 2; and severe, 3) will be used.^[25]^ Using 4 weeks of TNSS scores, we will analyze the differences in the effects of SCRT and cetirizine, and the duration of the effects of each medication.

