### Statistical analysis

2.11

An independent statistician who is blinded to the randomized allocation of participants will carry out the statistical analysis. Measured variables will be assessed using the full analysis set based on intention-to-treat principles, including all randomized participants who completing the trial without violating any of the exclusion criteria and for whom a complete set of data is available. The per-protocol analysis set will be used for the sensitivity analysis.

The demographic characteristics and baseline data of both groups will be summarized by means and standard deviations for the continuous variables, and frequencies and percentages will be presented for categorical variables. Baseline differences between groups will be assessed using independent *t* tests or Mann–Whitney *U* tests for continuous variables, and the chi-squared test or Fisher exact test for categorical variables. Differences in the primary and secondary outcomes will be analyzed using one-sided independent *t* tests. To demonstrate noninferiority, we will check whether the lower limit of the 2-sided 95% CI of the difference of the primary outcome between the 2 groups is greater than the noninferiority margin. The analysis will be presented as a difference with an associated 95% CI. To determine whether statistically significant differences exist between the groups, differences in the primary and secondary outcomes will be analyzed using a mixed effects model for repeated measurement. Subgroup analyses will also be conducted to investigate the difference in treatment effect according to the type of cold–heat pattern identification questionnaire, each symptoms of AR, and the results of Nasal Endoscopy Index. The level of significance will be set at 0.05 (2-tailed), and all analyses will be performed using SAS (V.9.4; SAS Institute).

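### The week-2 TNSS comparison and its noninferiority interval are described without baseline adjustment, although a baseline score is collected and adjusting for it costs one degree of freedom

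*Protocol article*

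**What the plan says.** The abstract fixes the primary outcome: "The primary outcome will be the mean change in the total nasal symptom score from baseline to week 2". It lists the collection points: "Data will be collected at baseline, at week 2, and at week 4 after random allocation". A change from baseline needs a baseline TNSS for every patient, so the covariate is collected in any case.

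Section 2.6.1 adds how the score is obtained: "TNSS will be recorded in participants’ diaries every day before bedtime using a mobile application".

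The Statistical analysis section (2.11) describes three things that bear on this point:

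- Primary and secondary outcomes are compared by independent t tests, and noninferiority is read from the two-sided 95% CI of the between-group difference in the primary outcome. No covariate is mentioned for either.
- The same outcomes are also analysed with a mixed effects model for repeated measurement, given as the way to establish whether the groups differ significantly. Its covariates are not stated, and the text does not say whether the t test and interval or the mixed model is primary.
- On baseline itself: "Baseline differences between groups will be assessed using independent" t tests or Mann–Whitney tests for continuous variables, with corresponding tests for categorical ones.

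The Sample size section (2.10) sets 12 evaluable patients per group and recruits 15 per group to allow for 20% dropout.

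**The concern.** A t test on change scores subtracts the whole baseline value, as if week-2 TNSS rose one point for each point of baseline. The true slope is normally below one. Two consequences follow in a small trial. The estimate is less precise than one that fits the slope, and a chance difference between the arms at baseline is over-corrected rather than removed.

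The planned baseline tests do not help. In a randomized comparison any baseline difference is due to chance, and a p-value for it leaves the treatment estimate as it was.

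At stake is the width of the interval on which noninferiority is to be read, and the quality of the estimate that the article's Discussion wants as a basis for a full-scale trial.

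**Working it through.** **Inputs.** From section 2.10: 12 evaluable per group, 20% dropout, 15 recruited per group. From the abstract: 1:1 allocation and change from baseline to week 2. Assumed, because the documents give no value: the correlation r between baseline and week-2 TNSS, taken as 0.3 to 0.9, with equal SD at both times.

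**The plan's own figure.** 12 / (1 − 0.20) = 15 per group, 30 in total. This reproduces. No power, SD or effect size is stated, so there is no power figure to check.

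**Variance of the two estimators**, per patient, in units of SD²:

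- Change score: 2(1 − r)
- Baseline-adjusted (ANCOVA): 1 − r²
- Ratio: (1 − r²) / [2(1 − r)] = (1 + r)/2
- Estimating the slope costs a factor of about 1 + 1/(N − 4). At N = 24 this is 1 + 1/20 = 1.05.

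95% CI half-width = t × √(2 × variance / 12), with t = 2.074 on 22 df for the change score and 2.080 on 21 df for ANCOVA (variance including the factor 1.05).

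| r (assumed) | (1 + r)/2 | × 1.05 | Variance saved | Half-width, change score (SD) | Half-width, ANCOVA (SD) |
|---|---|---|---|---|---|
| 0.3 | 0.65 | 0.68 | 32% | 1.00 | 0.83 |
| 0.5 | 0.75 | 0.79 | 21% | 0.85 | 0.75 |
| 0.7 | 0.85 | 0.89 | 11% | 0.66 | 0.62 |
| 0.9 | 0.95 | 0.9975 | about 0% | 0.38 | 0.38 |

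The break-even is (1 + r)/2 × 1.05 = 1, or r ≈ 0.905. Above it the adjusted analysis loses slightly, by at most 5% of the variance (r = 1).

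**Chance imbalance.** At 12 per arm the standard error of the baseline difference is √(2/12) = 0.41 SD. An imbalance beyond 0.5 SD in either direction lies 0.5/0.41 ≈ 1.22 standard errors out and has a probability of about 22%. Given an imbalance d, the change-score difference is displaced by (1 − r)d. With d = 0.5 SD and r = 0.5 that is 0.25 SD. ANCOVA removes this displacement up to the error in its slope.

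**If weekly diary means were intended.** With equal correlation r_w between days within a week and r_b between the two weeks, a 7-day mean has variance (1 + 6r_w)/7, and the correlation between the weekly means is r_b divided by that variance.

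- r_w = 0.5, r_b = 0.3: variance 0.571, correlation 0.525, ratio (1.525/2) × 1.05 = 0.80.
- r_w = 0.8, r_b = 0.6: variance 0.829, correlation 0.724, ratio (1.724/2) × 1.05 = 0.91.

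Adjustment would then still save about 10% to 20%.

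**The case against.** The strongest objection is that the t test is not the only planned analysis. The mixed model covers the primary outcome too and may already include baseline, and an article can leave model covariates to the full protocol or SAP. This stands in part: one cannot say that the trial will make no adjusted comparison. It does not settle the point, because the noninferiority rule is not linked to that model. Nor is a repeated-measures model adjusted by default. If baseline is simply one of the responses and group means are free at every time, then with complete data its change contrast equals the unadjusted change-score difference.

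A second objection is that harm is limited. Under randomization the change-score comparison is unbiased, and regression to the mean affects both arms equally in expectation. This is also a feasibility trial with a rule-of-thumb sample size and no power claim, and no section says that its SD will size the next trial. All of that stands. The loss is one of precision and of exposure to chance imbalance.

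Three stronger readings are tempting, and the documents do not support them:

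- *The abstract and section 2.6.1 conflict on the endpoint.* Section 2.6.1 says "Using 4 weeks of TNSS scores, we will analyze the differences in the effects of SCRT and cetirizine". The same sentence goes on to name a second purpose, how long the benefit of either drug lasts. The four weeks therefore also serve the off-treatment duration aim, and that section sets no time point against week 2.
- *Single-day ratings are compared, so most of the information is discarded.* Against a single-day change score, weekly means plus adjustment would bring the variance ratio to between 0.31 and 0.52 under the assumed correlations. No section says that single days are used, and the diary window is detail that an article may leave out.
- *A run-in diary exists and is ignored.* The design is described as follows: "It consists of a week run-in period after screening, 2 weeks of medication, and 2 weeks of follow-up after medication is stopped". Whether the diary is kept in the run-in week is not stated either way, and the schedule table is not shown.

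**Conclusion.** The point holds in limited form. The t test and the noninferiority interval are described without a baseline term, the mixed model's use of baseline is left open, and the baseline significance tests correct nothing. Adjustment would reduce the variance of the week-2 difference by about 11% to 32% at 12 per arm for r from 0.7 to 0.3, which narrows the 95% CI by roughly 5% to 17% (0.62/0.66 and 0.83/1.00). The gain is practically nil near r = 0.9. The size rests wholly on the assumed correlation and on equal SDs at the two times. The direction holds for any r below about 0.90. This is an improvement in efficiency that needs no new data; it does not make the planned comparison invalid.

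**What to change.** In section 2.11:

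- Name one primary analysis of TNSS at week 2 with baseline TNSS as a covariate. ANCOVA will do, or the already planned mixed model with its week-2 contrast.
- Report the treatment difference and its two-sided 95% CI from that model, and use that interval for the noninferiority check in place of the unadjusted t test.
- Delete the between-group significance tests at baseline and keep the descriptive table.

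The cost is a few sentences and one residual degree of freedom (22 to 21 at 24 patients).

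As an optional addition, since TNSS is scored daily, state that several diary days are averaged at week 2, and also at baseline if diaries are kept during the run-in. This adds precision if single days were otherwise meant. If averaging is already planned, it needs only to be stated.

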**Discussion::**

The findings of this study are expected to provide the basis for a full-scale randomized controlled trial to confirm the safety and effectiveness of SCRT for the treatment of nasal symptoms in patients with AR patients not controlled by conventional therapy.

**Trial registration::**

This study has been registered at the Korean National Clinical Trial Registry, Clinical Research Information Service (KCT0002380).

## Introduction

1

Allergic rhinitis (AR) is an inflammatory disease caused by an immunoglobulin E (IgE)-mediated response and is characterized by one or more typical nasal symptoms of rhinorrhea, nasal congestion, sneezing, and nasal itching, as well as non-nasal symptoms such as tears, ocular hyperemia, itching around the eyes, and itchy palate.^[1,2]^

AR is a common condition, and the prevalence has been increasing over the last decade. The prevalence of AR is 10% to 30% of the world's population; the prevalence is 11.9% to 30.2% in the United States^[3]^ and around 22.7% in European countries.^[4]^ Although the nasal symptoms of AR are not threatening to life, the symptoms can affect social and daily activities such as sleep, learning, and work, ultimately generating considerable medical expenses.^[5,6]^ Moreover, when AR occurs repeatedly, it becomes difficult to treat and can cause complications such as bronchial asthma, rhinosinusitis, conjunctivitis, and otitis media.^[7]^

The general treatment and management of AR aims at relieving symptoms quickly by avoiding the causes of allergens and managing symptoms to minimize recurrence.^[8]^ However, most people cannot completely avoid allergens due to industrialization, modernization, and urbanization of residence.^[9–12]^ Conventional therapies such as antihistamines, decongestants, and glucocorticoids are used to control AR symptoms, but there are the risks of adverse effects with long-term use, and the effects do not persist when the medication is stopped. Moreover, some AR patients cannot take medication because of its side effects.^[13]^

Due to the limited success of conventional medical treatments, various complementary and alternative medicines are currently used in clinical settings. In East Asian countries, complementary and alternative medicine in the form of traditional herbal medicine is widely used to treat AR.^[14]^ Socheongryong-tang (SCRT, known as Sho-seiryu-to in Japanese, Xiao-Qing-Long-Tang in Chinese) is an herbal formula broadly used throughout East-Asian countries,^[15]^ and is approved by the Korean Ministry of Food and Drug Safety (MFDS) for bronchitis, asthma, rhinitis, and cold-related symptoms including rhinorrhea and cough.^[16]^ According to previous studies, SCRT has anti-inflammatory and anti-allergic properties.^[17,18]^ A survey of Korean physicians found that SCRT is the most widely used herbal prescription for the treatment of AR.^[19]^ There is evidence that SCRT is more effective than placebo in reducing nasal symptoms associated with AR.^[20]^ However, there is no evidence that SCRT is a viable alternative to conventional therapies, especially for AR patients whose symptoms are not controlled by conventional medication.

Antihistamines are the first-line treatment in AR.^[21]^ Cetirizine (Zyrtec Tab, Korea UCB Co., Ltd. Seoul, Korea) was selected as the control for this study because it is the most commonly used antihistamine.^[22]^ Cetirizine is a specific and long-acting histamine H1 receptor antagonist. It has marked anti-allergic properties and inhibits eosinophil chemotaxis during the allergic response, and has shown efficacy and safety in the treatment of patients with AR.^[23]^

The purpose of this study is to validate a protocol for comparing the effectiveness of SCRT with that of conventional medicine. The findings of this study are expected to provide a base for large-scale randomized controlled trials of the comparative effectiveness of SCRT for the treatment of AR, and may consequently serve to improve future treatment strategies for this condition.

## Methods

2

### Objectives

2.1

This study is a feasibility trial to assess the safety and clinical effectiveness of SCRT on the AR, in comparison with cetirizine.

### Trial design and setting

2.2

This is a randomized two-parallel-arm open-label cetirizine-controlled comparative effectiveness study. This study will be conducted at Woosuk Korean Medicine Medical Center, Jeonju, Republic of Korea. The study has 2 arms: the SCRT treatment group and the cetirizine control group. A total of 30 participants will be recruited for this trial. Cetirizine will be used as an active control to compare the effectiveness of SCRT on AR patients whose symptoms are not controlled by conventional medication. The total study period will be 5 weeks. It consists of a week run-in period after screening, 2 weeks of medication, and 2 weeks of follow-up after medication is stopped.

The detailed design is summarized in Fig. 1 and Table 1. The study protocol (version 1.3) follows the Standard Protocol Items: Recommendations for Interventional Trials (SPIRIT) guidelines (see Additional File 1).

**Figure 1 F1:**
[figure not shown]
Flowchart describing the study plan. SCRT = Socheongryong-tang.

**Table 1 T1:**
[figure not shown]
Schedule of enrolment, interventions, and outcome measurements for a randomized controlled trial assessing the safety and clinical effectiveness of SCRT in allergic rhinitis compared with cetirizine.

### Recruitment

2.3

The trial will be advertised on the hospital bulletin board, local newspapers, and websites used by local community residents. If necessary, potential participants who express a desire to enroll will be provided information about the study or pre-screened for eligibility before the first visiting to the hospital, by clinical trial coordinators via a telephone. Written informed consent will be obtained from all study participants prior to enrolment, and participants may decline to participate or withdraw at any time without disadvantage.

### Study participants

2.4

The inclusion and exclusion criteria of participation in this study are set according to the Allergic Rhinitis and its Impact on Asthma (ARIA) guideline criteria for persistent AR.

#### Inclusion criteria

2.4.1

Participants will be included in this study if they meet the following criteria:

(1)Either male or female, 19–65 years of age(2)Persistent AR patient, meaning all of the following:A.Presence of 2 or more symptoms of AR (rhinorrhea, nasal congestion, sneezing, and nasal itching)B.Symptoms existing 4 days a week for more than 4 weeksC.Persistent AR with a history of more than 2 years, with symptoms not controlled by antihistamine treatment(3)Positive allergic reaction in the multiple allergen simultaneous test (MAST)(4)Voluntary participation in this study and signing of the patient consent form after explanation of the purpose of the study.

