## Discussion

3

This study is a feasibility trial to assess the safety and clinical effectiveness of SCRT in AR patients who are not well-controlled by conventional therapies.

In this study, we will enroll patients with a history of at least 2 years of persistent AR. The 2 year criterion was chosen based on the inclusion criteria of previous studies of uncontrolled AR patients.^[31,32]^ The strict meaning of “uncontrolled” can be “persistence of severe symptoms,” but in this study we interpreted it as, “the symptom frequently occurs despite steady treatment.” As in previous studies, we considered that 2 years of AR history is long enough to assess the success of conventional therapies. Thus, patients with a history of at least 2 years of persistent AR form the target population in this study.

This study was designed to refine treatment regimen of SCRT, and to evaluate whether SCRT could be an alternative to conventional therapy. In East Asia, SCRT has been used for the treatment of respiratory diseases such as the common cold, asthma, and allergic rhinitis, and studies are being conducted to evaluate its effectiveness.^[20,33,34]^ In this study, we apply cold–heat pattern identification diagnosis, which is a basic diagnostic tool for Korean Medicine.^[35]^ SCRT showed more effectiveness in relieving common cold symptoms in patients who had a cold pattern than in patients who had a hot pattern.^[33]^ Thus, we assume that the effect of SCRT will be different according to cold and heat pattern. By subgroup analysis of cold–heat pattern, we can draw conclusions about the use of pattern identification for prescription of herbal medicine. In addition, we will report the changes of each symptom of allergic rhinitis to find possible indications for SCRT as a complement to cetirizine.

In this study, blinding of the participants is impossible because of the use of different types of drugs (granules for SCRT and tablets for cetirizine). In pragmatic RCTs, although the participants and investigators are often un-blinded, it is still desirable and often possible to blind the assessors or to obtain an objective source of data for evaluation of outcomes.^[36]^ However, in the case of AR, the subjective symptoms of the patient are recommended as the primary outcome. In this study, serum IgE and the Nasal Endoscopy Index, evaluated by 2 independent assessors, are added as a secondary variable to minimize bias.

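### Noninferiority to cetirizine in patients selected as uncontrolled on antihistamines cannot show that SCRT works or can replace effective conventional therapy

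*Protocol article*

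**What the plan says.** All of the following is in the protocol article.

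- **Population.** Section 2.4.1, criterion 2C, requires "Persistent AR with a history of more than 2 years, with symptoms not controlled by antihistamine treatment". The Discussion explains that uncontrolled is not read strictly as persistent severe symptoms but as "the symptom frequently occurs despite steady treatment".
- **Washout.** Exclusion criterion 1C (section 2.4.2) rules out antihistamine use in the preceding week, and section 2.2 adds a one-week run-in after screening.
- **Control.** According to the Introduction, cetirizine "was selected as the control for this study because it is the most commonly used antihistamine" and "has shown efficacy and safety in the treatment of patients with AR". Section 2.2 states the pairing with the population openly: "Cetirizine will be used as an active control to compare the effectiveness of SCRT on AR patients whose symptoms are not controlled by conventional medication". There are two arms, open label, with neither a placebo nor an untreated arm.
- **Inference.** The words "To demonstrate noninferiority" open the decision rule in section 2.11, and success is defined as follows: "lower limit of the 2-sided 95% CI of the difference of the primary outcome between the 2 groups is greater than the noninferiority margin". A mixed model to look for differences between the groups is planned in that section as well.
- **Aim.** The Discussion says the study was designed, among other things, "to evaluate whether SCRT could be an alternative to conventional therapy".

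**The concern.** A noninferiority result says something about efficacy only if the control is itself effective, by a known amount, in the patients studied. Here patients are selected because the control's drug class did not control their symptoms. The evidence cited for the control comes from allergic rhinitis patients without that selection, and the trial has no arm that could reveal whether cetirizine works in the patients enrolled.

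If cetirizine's effect in these patients is smaller than the margin, a product with no effect at all meets the noninferiority rule more often than the nominal 2.5%. The reader would then be told that SCRT is not worse than a standard antihistamine, and could take this as support for SCRT as an alternative to conventional therapy, when the data are equally consistent with neither treatment doing much.

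**Working it through.** **Plan's own figure.** Section 2.10 takes 12 per arm from a rule of thumb and allows 20% dropout: 12 / (1 − 0.20) = 15 per arm, 30 in total. This reproduces. There is no power calculation to reproduce.

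**Where the control's effect is supported.** The Introduction supports cetirizine in allergic rhinitis patients generally. Criterion 2C selects patients not controlled on its class. No statement in the article connects the two, so the residual effect has to be treated as unknown.

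**Inputs for the illustration.** The article gives no margin, SD or cetirizine effect, so all three are assumptions, in SD units of the TNSS change:
- *n* = 12 per arm (section 2.10, number before the dropout allowance), so df = 22
- margin *M* = 0.5 or 1.2 SD (assumed; 1.2 SD is about the margin that gives 80% power at 12 per arm if the true difference is zero)
- residual cetirizine effect *c* = 0, 0.2 or 0.3 SD (assumed)
- SCRT effect = 0 (inert)

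**Formula.** Code the difference so that positive values favour SCRT. The true difference is then −*c*, and noninferiority is declared if the lower 95% limit exceeds −*M*.

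- Standard error = √(2/12) = 0.408 SD
- Critical value t(0.975; 22) = 2.074
- ncp = (*M* − *c*) / 0.408
- P(inert product passes) = 1 − F(2.074; df 22, ncp), with F the noncentral t distribution function

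| Margin *M* | Residual effect *c* | ncp | P(inert SCRT passes) |
|---|---|---|---|
| 0.5 SD | 0 | 1.225 | 21.5% |
| 0.5 SD | 0.2 SD | 0.735 | 10.4% |
| 0.5 SD | 0.3 SD | 0.490 | 6.8% |
| 1.2 SD | 0 | 2.939 | 80% |
| 1.2 SD | 0.2 SD | 2.449 | 65% |
| 1.2 SD | 0.3 SD | 2.205 | 56% |
| either | *c* = *M* | 0 | 2.5% |

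The rate is above 2.5% whenever *c* is below *M*, and below 2.5% whenever *c* is above *M*. The 80% entry follows from how the 1.2 SD margin was chosen: when *c* = 0, an inert product and an equally effective one have the same true difference, zero. What it shows is that the test cannot tell these two situations apart.

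**Superiority, by the same method.** Setting the threshold at 0 instead of −*M*, an inert SCRT beats an inert cetirizine in 2.5% of trials. If cetirizine keeps a 0.25 SD effect, the rate is 0.5%. The choice of comparator does not inflate this error. None of these figures includes bias from open-label self-scoring.

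**Precision.** The 95% CI half-width is 2.074 × 0.408 = 0.85 SD at 12 per arm. At 15 per arm it is 2.048 × √(2/15) = 0.75 SD.

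**The case against.** Four arguments count against the point.

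1. *This is a feasibility trial, and confirmation is left to a full-scale study.* True, and the aim is worded as whether SCRT could be an alternative. This softens the consequence. But section 2.11 plans a formal noninferiority conclusion, which a trial limited to feasibility would not need.

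2. *Cetirizine may still work in these patients.* This stands in part. The Discussion's definition of uncontrolled allows partial response, and participants enter after at least a week without antihistamines, so a partial responder could improve again on cetirizine. A reader might infer from criterion 2C that the control's effect is close to zero; the documents do not support that. They support only that the effect is unknown and possibly reduced, which is enough to undermine the noninferiority inference.

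3. *Beating cetirizine would be informative.* This stands. A reader might infer that no comparison with cetirizine could show that SCRT works. If cetirizine is at worst no better than placebo, true superiority over it does imply an SCRT effect in these patients, and they are the declared target population. Two limits remain. The result would not carry over to allergic rhinitis in general, because the sample is selected against the control's class. And TNSS is scored by patients who know their treatment. The article acknowledges the lack of blinding and adds serum IgE and assessor-blinded endoscopy, but only as secondary outcomes.

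4. *The size depends on the margin.* It does. The high figures at 1.2 SD largely reflect a wide margin, which is why the 0.5 SD results are shown with them. The direction does not depend on the choice.

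**Conclusion.** The point holds for the noninferiority conclusion and for generalisability. As planned, finding SCRT noninferior would not establish that it has an effect, or that it can stand in for conventional therapy that works. This follows from three things that the article itself fixes: eligibility, comparator and decision rule.

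How often an inert product would pass cannot be determined from the documents. Over the assumed ranges it runs from 6.8% to 80% at 12 per arm, against 2.5% when the residual cetirizine effect equals the margin. If the residual effect were larger than the margin, there would be no inflation.

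The point does not extend to a superiority finding in antihistamine-uncontrolled patients, which remains interpretable subject to the open-label scoring and the small sample. It is worth correcting before the analysis but does not call the trial's arms or population into question.

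**What to change.** Keep the population and the two arms, and change the following.

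- **Section 2.11:** delete the noninferiority test. Report the between-group difference in TNSS change with its 95% CI, as an estimate.
- **Sections 2.1 and 2.2:** restate the question as SCRT versus cetirizine, each started after antihistamine washout, in patients uncontrolled on antihistamines. Avoid describing the control arm as continuing an antihistamine, because exclusion 1C means nobody is.
- **Discussion:** limit the conclusion about SCRT as an alternative to conventional therapy to that comparison and that population.
- **Planning of the full-scale trial:** state that any noninferiority claim there needs one of three things: a justified cetirizine effect and margin in antihistamine-uncontrolled patients, a placebo reference, or an unselected population.

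The cost is protocol wording only, with no change to recruitment, visits or data collection. The downside is a narrower claim.
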